### Statistical issues

#### Sample size

The randomised trial in our study will be a non-inferiority effectiveness trial. Based on our pilot study [25], we anticipate the probability on preterm birth within 7 days in the group of women with a negative fibronectine test and a cervical length 10-30 mm to be 5%. We need 220 fibronectin negative women in the cohort (110 per arm) to assure with 80% power that in case of non-inferiority the upper limit of the 95% one-sided CI for the difference in the proportion of preterm deliveries < 7 days will be within a prespecified boundary of 7.5%. According to our pilot we will need a cohort of approximately 660 women [25].

#### Data analysis

The results of the randomised trial will be analyzed according to the intention to treat principle. We will analyze costs and effects of a strategy based on fibronectin measurement and cervical length, in which only fibronectin positive women will be transferred to a perinatal center and/or and treated. Costs and effects of this strategy will be compared to a strategy in which these women will be transferred and treated merely based on a clinical diagnosis by e.g. vaginal examination and/or cervical length measurement.

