### Procedures, recruitment, randomisation and collection of baseline data

Women meeting the eligibility criteria will be informed and invited to participate in the study and asked for written informed consent. At study entry baseline demographics, obstetric and medical history will be recorded. Before cervical length measurement, women will be tested for fibronectin. Therefore a sample of cervicovaginal secretion will be taken by rotating a swab in the posterior vaginal fornix for 10 seconds. Analysis will be performed using the FullTerm TLi_IQ _system of Hologic [26].

Women with a cervical length below 10 mm and women with a cervical length between 10-30 mm in combination with a positive fibronectin test will be treated with tocolysis. These women are considered to be at high risk for preterm delivery. Women with a cervical length above 30 mm will be treated according to the discretion of the physician. Women with a cervical length between 10-30 mm and a negative fibronectin test are considered to be at low risk, they will enter a double blind trial in which they will be randomised by a central web-based system between tocolytics or placebo (1:1). Details of delivery and maternal assessments during pregnancy of all women are recorded in case record forms (CRF) that are accessible through a closed part of a central website. All data will be collected, coded and processed with adequate precautions to ensure patient confidentiality.

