### Interventions

All high risk women will receive tocolytics according to local protocol. Fibronectin negative women with a cervical length between 10-30 mm will be randomly allocated to tocolytics or placebo (figure 1). Active treatment will be performed with the calcium channel blocking agent nifedipine with a total daily dose between 80 and 120 milligrams for 48 hours. Active drug and placebo will be administered orally at the same volume and rate. Corticosteroids will be administered at the discretion of the attending physician.

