### Economic evaluation

The aim of the economic evaluation is to assess whether fibronectin testing as a triage for women with threatened preterm labor is cost-effective. For the cost analysis we distinguish cost within the antenatal period, during delivery and childbirth and within the postnatal period. As the study will be performed from a societal perspective, three cost categories will be included: direct medical costs, direct non-medical costs and indirect costs. Volumes of health care resource use during the index admission are measured prospectively alongside the clinical study in all participating centers as part of the CRF. Questionnaires addressing health related quality of life will be administered in a random subsample.

If the randomised trial indicates that a particular subgroup of women does not benefit from treatment with tocolytics, the economic analysis will be a cost-minimization analysis. If tocolysis and transferring low risk women would not be necessary, the costs of risk assessment (int.al. fibronectin testing) of the whole cohort of women will be compared to the potential cost saving. Furthermore, scenario analyses for relevant subgroups will be performed. Before analyzing the data from the study, a detailed cost analysis model will be developed.

The trial results will be incorporated in a diagnostic model to compare a risk assessment strategy for women with threatening preterm labor within current practice, which does not include additional risk assessment with fibronectin.

The study design will enable us to compare the costs and effects of the following strategies:

I. transfer and treat all women with threatening preterm labor

II. transfer and treat women based on the results of fibronectin measurement. As we also measure cervical length, we can also evaluate the following strategies:

III. transfer and treat women based on the results of cervical length measurement

IV. transfer and treat women based on a combination of cervical length measurement and fibronectin measurement

V. sequential combinations, for example first cervical length measurement, and fibronectin measurement in a part of that women, or vice versa.

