In our cohort, we will obtain data on the moment of delivery in women treated with tocolytics and not treated with tocolytics. In addition to our cohort data, we will obtain data from medical literature on the occurrence of neonatal mortality and morbidity in relation to duration of pregnancy, both with and without treatment of corticosteroids. We will use this to calculate the expected neonatal mortality and morbidity for each of the five strategies mentioned above.

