## Discussion

In women with clinical signs of threatened preterm labor, fibronectin can discriminate between those at low risk and high risk for immediate preterm delivery. Since treatment of low risk women might be unnecessary, testing for fibronectin is thought to be a cost effective strategy. It may protect mother and fetus from possible side effects of tocolytics and corticosteroids, lessen burden of perinatal centers and decrease stress and anxiety for the families. So far, no randomised trial has shown beneficial effects of fibronectin testing for women presenting with threatened preterm labor, despite its high negative predictive value. Although the use of fibronectin tests for these women is already implemented in some clinics and even incorporated into guidelines [27], neither its safety as a triage instrument, nor its cost effectiveness has been established.

We decided to use a fixed protocol to translate the test results into a management strategy with nifedipine, to out rule the influence of individual physicians. Nifedipine has not yet been tested against placebo as a tocolytic drug, though both the Cochrane Collaboration [28] and the Dutch Society of Obstetrics and Gynaecology [2] recommend calcium antagonists as first choice. It is unlikely that using another tocolytic drug would lead to different outcomes of this trial, since fibronectin negative women have a low a priori probability of delivering within 7 days after the test. So even though we randomize on therapy level, this trial will evaluate fibronectin testing and cervical length measurement for women with threatened preterm labor.

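### The claim that the design can compare strategies I–V is too broad: only fibronectin-negative women at 10–30 mm are randomised, and the combined strategy under Data analysis departs from the triage rule

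*Protocol article*

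**What the plan says.** All references are to the protocol article.

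- **Triage rule.** Under Procedures, the treated group is "Women with a cervical length below 10 mm and women with a cervical length between 10-30 mm in combination with a positive fibronectin test". The Abstract gives the same rule, and Interventions adds "All high risk women will receive tocolytics according to local protocol".
- **Randomised group.** Interventions: "Fibronectin negative women with a cervical length between 10-30 mm will be randomly allocated to tocolytics or placebo".
- **Long cervix.** Procedures: "Women with a cervical length above 30 mm will be treated according to the discretion of the physician". The Abstract refers to local protocol instead. Either way these women are not randomised.
- **Strategy to be evaluated.** Data analysis describes a strategy built on both tests, "in which only fibronectin positive women will be transferred to a perinatal center and/or and treated".
- **Claim about the design.** Economic evaluation: "The study design will enable us to compare the costs and effects of the following strategies". The list is: treat all (I), fibronectin alone (II), cervical length alone (III), both combined (IV) and sequential combinations (V).
- **Inputs.** Economic evaluation: "In our cohort, we will obtain data on the moment of delivery in women treated with tocolytics and not treated with tocolytics". The literature is to supply neonatal mortality and morbidity by duration of pregnancy, with and without corticosteroids.
- **Conclusion drawn.** Discussion: "this trial will evaluate fibronectin testing and cervical length measurement for women with threatened preterm labor".

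**The concern.** Two things do not fit together.

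First, a combined strategy that treats only fibronectin-positive women leaves fibronectin-negative women below 10 mm untreated. The study treats all of them. The strategy to be evaluated is therefore not the one the study applies, and one of its groups has no data under the management it assumes.

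Second, comparing two strategies means knowing the outcome with and without treatment in every group where they differ. The design supplies both, protected by randomisation, in one group only. The Economic evaluation nevertheless presents all five strategies as comparable by virtue of the design.

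Cost-effectiveness of triage is the stated aim in the Abstract, the Aims and the Economic evaluation. If randomised and assumed inputs are not kept apart, results for some strategies will appear to carry trial-level evidence that they do not have.

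**Working it through.** **Size of the randomised group.** The Sample size section gives 110 per arm, 220 in total, from about 660 women. With the pilot rate 1/19 = 5.26% in both arms, margin 7.5 points, one-sided α 0.05 and power 80%, the unpooled normal formula gives

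n = (1.645 + 0.842)² × 2 × 0.0526 × 0.9474 / 0.075² ≈ 109.6, so 110 per arm.

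The rounded 5% gives 105, and power at 110 is then 81.8%. The figure is not in dispute. It gives 220/660 = 33% randomised and 440/660 = 67% not.

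**What each group lets one observe under the protocol.**

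| Group | Cervical length | Fibronectin | Treated outcome | Untreated outcome |
|---|---|---|---|---|
| A | below 10 mm | positive | observed | never |
| B | below 10 mm | negative | observed | never |
| C | 10–30 mm | positive | observed | never |
| D | 10–30 mm | negative | randomised | randomised |
| E | above 30 mm | positive | physician's choice | physician's choice |
| F | above 30 mm | negative | physician's choice | physician's choice |

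**What each strategy needs.** The difference in effect between two strategies is the sum, over the groups where they differ, of (group share) × (treated outcome − untreated outcome).

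- *I, treat all:* needs treated outcomes in E and F, seen only in women a physician chose to treat.
- *II, fibronectin alone:* needs the untreated outcome in B, which is never observed. It also needs treated outcomes in E and untreated outcomes in F, both under discretionary treatment.
- *Data analysis strategy, read literally:* also needs the untreated outcome in B.
- *III, cervical length alone:* the article gives no cut-off. If all women at or below 30 mm are treated, A–D are treated and nothing unobserved is needed there. A cut-off within 10–30 mm would leave some of C untreated, which is never observed.
- *IV, both tests, in the form the study applies:* A, B and C treated, D untreated.
- *V:* depends on the sequence chosen.

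**The supported contrast.** Take IV as the study's rule and III as treating everyone at or below 30 mm, with women above 30 mm managed alike under both. The two then differ only in D, so the difference is about 0.33 × (treated − untreated outcome in D), which the trial estimates with randomisation.

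**Whether outside data fill the gaps.** The literature inputs turn duration of pregnancy into neonatal outcome. They do not supply the effect of tocolysis on time to delivery in groups A–C. The Discussion also states that nifedipine has not yet been compared with placebo as a tocolytic, so on the article's own account there is no placebo-controlled nifedipine effect to bring in.

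The article gives no sizes for groups A, B, C, E and F separately, so the effect on strategies I and II cannot be quantified from it.

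**The case against.** The other side has several good points.

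- **Modelling is already announced.** The Economic evaluation says that trial results go into a diagnostic model, that a detailed cost model will be developed before the data are analysed, and that scenario analyses will be run. Details may sit in the full protocol. This stands, and missing model detail is not the complaint. What remains is that the article credits the design with a comparison that depends on assumptions.
- **A modelled strategy may differ from the rule applied.** The Data analysis wording may be shorthand for the 10–30 mm band. That is possible, but the text does not say so, and read literally it needs an unobserved outcome.
- **The core comparison is sound.** The contrast in the randomised group stands. So does the cost-minimisation route, which sets the cost of testing the whole cohort against savings in low-risk women and needs no untreated outcome below 10 mm. A reader might infer that none of the strategies can be estimated; the documents do not support that.
- **No crude contrast is stated.** A reader might infer that treated and untreated women will be pooled across the cohort, making tocolysis look harmful. The article says only that delivery times will be obtained in both, and the randomised group itself contains both. The wording leaves the source of the effect open but does not announce a pooled comparison.
- **Confounding is the wrong word for A–C.** By protocol these groups have no untreated women, so the defect is a missing comparator. Confounding by indication applies above 30 mm, and would apply to a pooled contrast if one were made.
- **The aim is limited to low-risk women.** A reader might object that, with no fibronectin-positive woman randomised, the trial cannot separate a useful test from a drug that works in nobody. The Aims confine the intended policy to low-risk women, and withholding treatment there can be tested without randomising others. The point supports narrowing the closing claim of the Discussion and is not a design error.

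**Conclusion.** The point holds in a limited form. The Data analysis strategy conflicts with the triage rule in the Abstract, Procedures and Interventions and must be reconciled with it. I take no view on which rule is clinically right. The claim that the design enables comparison of strategies I–V is too broad for at least I and II. About 33% of the planned cohort carries a randomised contrast, and about 67% does not. This assumes that recruitment follows the pilot-based 220 of 660 and that the treatment rules are followed as written.

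A reader might try to size the bias from the Background: 15% and about a third delivering within 48 hours, against under 5% within 7 days, giving ratios of 15/5 = 3 and 33/5 ≈ 6.7. These are ratios of prognosis between groups, with mixed time horizons and a 15 mm cut-off from an external study. They do not measure the bias of any planned analysis, and I give no bias figure.

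The primary outcome, the randomised comparison and the sample size are untouched.

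**What to change.** 1. Reconcile Data analysis with Procedures and Interventions. Say whether the combined strategy follows the study's triage rule or is meant to differ from it, and how women below 10 mm are handled in it.
2. In the Economic evaluation, state that the effect of tocolysis on time to delivery is taken from the randomised group and not from treated versus untreated women across the cohort.
3. For groups without a comparator, keep the observed treated outcomes and apply an explicit scenario range for the untreated ones, for example from no effect of tocolysis to the effect estimated in the trial.
4. Replace the claim that the design enables all five comparisons. Label the strategies that depend on groups outside the randomised one, at least I and II, as resting on modelling assumptions. Check III and V once their cut-offs and sequences are fixed.
5. Limit the trial's own conclusion in the Discussion to fibronectin-negative women at 10–30 mm.

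The cost is wording and scenario runs in a model not yet built, with no new patients. The downside is wider stated uncertainty for the extrapolated strategies.

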#### Interim analysis

After 100 fibronectin negative, low risk women have entered the randomised trial, an interim analysis will be performed by an external independent safety committee. Interim analysis will be performed on the primary outcome only, e.g. percentage of preterm deliveries within 7 days after fibronectin testing. If there is a significant difference between the groups treated with tocolytics and placebo, the independent safety committee will decide about further unblinding of the interim results and (dis)continuation of the trial.

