**Methods/Design:**

We will investigate a prospective cohort of women referred to a perinatal centre for spontaneous threatened preterm labor between 24 and 34 weeks with intact membranes. All women will be tested for fibronectin and cervical length. Women with a cervical length <10 mm and women with a cervical length between 10-30 mm in combination with a positive fibronectin test will be treated with tocolytics according to local protocol. Women with a cervical length between 10-30 mm in combination with a negative fibronectin test will be randomised between treatment with nifedipine (intervention) and placebo (control) for 48 hours. Women with a cervical length > 30 mm will be managed according to local protocol. Corticosteroids may be given to all women at the discretion of the attending physician. Primary outcome measure will be delivery within 7 days. Secondary outcome measures will be neonatal morbidity and mortality, complications of tocolytics, costs and health related quality of life. The analysis will be according to the intention to treat principle. We anticipate the probability on preterm birth within 7 days in the group of women with a negative fibronectine test to be 5%. Two groups of 110 women will be needed to assure that in case of non-inferiority the difference in the proportion of preterm deliveries < 7 days will be within a prespecified boundary of 7.5% (one sided test, β 0.2, α 0.05). Data obtained from women with a positive and negative fibronectin tests in both the cohort study and the trial will be integrated in a cost-effectiveness analysis that will assess economic consequences of the use of fibronectin.

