The predictive capacity of fibronectin has been the topic of previous studies. Honest and co-workers published in 2002 a systematic review on the predictive capacity of fibronectin for preterm delivery [16]. They identified 40 studies reporting on symptomatic women. The summary likelihood ratio for a positive result was 5.4 (95% CI 4.4 to 6.7) for predicting birth within 7 to 10 days of testing, with a corresponding likelihood ratio for a negative result of 0.25 (95% CI 0.20 to 0.31). Therefore fibronectin testing might be able to reduce unnecessary treatment and subsequent costs. On the other hand, introducing fibronectin tests has not yet proven to reduce health care costs if the subsequent management is subject to physicians preferences [17-21]. In addition, high false positive rates may increase health care costs in the management of low risk women.

For cervical length measurement, the situation is different. This test is shown to predict preterm delivery in asymptomatic women at 20 weeks [22]. However, the accuracy of the test is only marginally evaluated in women with symptoms of preterm labor at a later gestational age [23]. Gomez et al. evaluated the predictive accuracy of a combination of fetal fibronectin measurement and cervical length measurement [24]. In their study, 15% of the women had cervical lengths below 15 mm, and one third of these women delivered within 48 hours. Among those with a cervical length between 15 mm and 30 mm (36% of the population), 25% had a positive fibronectin test, and 15% of this group delivered within 48 hours. Of the remaining 75% of the women, less than 5% delivered within 7 days. These results are comparable with our pilot study of [name] et al. Amongst 19 women with a cervical length between 10-30 mm and a negative fibronectin test, only 1 woman delivered within 7 days[25].

At present, fibronectin testing is not routinely used in The Netherlands. To assess the risk for threatened preterm labor, only cervical length is routinely measured[2]. This measurement is frequently used as an argument to transfer and treat women for threatened preterm labor, even if clinical symptoms are mild. Identifying women that are at high risk for preterm delivery could benefit from adding fibronectin testing. Therefore we will evaluate if adding fibronectin testing to cervical length measurement is a safe and cost-effective strategy as a triage for women with threatened preterm labor.

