### Outcome measures

The primary outcome measure is number of days to delivery truncated at 7 days after study entry. Secondary endpoints are neonatal mortality, neonatal morbidity, maternal morbidity (side effects of nifedipine), costs and health related quality of life.

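### The safety committee's formal interim analysis is limited to the primary outcome, so neonatal death, neonatal morbidity and maternal side effects fall outside it as written

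*Protocol article*

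**What the plan says.** The Interim analysis section of the protocol article plans one look, after 100 low-risk women have been randomised, by an external independent safety committee. Its scope is explicit: "Interim analysis will be performed on the primary outcome only". The action follows from a comparison of the arms: "If there is a significant difference between the groups treated with tocolytics and placebo, the independent safety committee will decide about further unblinding". The committee also decides whether the trial continues. The section gives no significance level, direction or boundary.

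Outcome measures lists what lies outside that scope: "Secondary endpoints are neonatal mortality, neonatal morbidity, maternal morbidity (side effects of nifedipine"), together with costs and quality of life. The section on follow-up of women and infants says that intensive-care admissions and complications of the newborn are recorded.

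The final analysis is a non-inferiority comparison. The difference in deliveries within 7 days must lie "within a prespecified boundary of 7.5" percent, and the Abstract gives the error rates as "one sided test, β 0.2, α 0.05".

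**The concern.** The article describes a single look by a body named a safety committee, and that look covers the efficacy outcome alone. The Background justifies the trial partly by severe side effects of tocolytics in mother and child, and the Discussion says nifedipine has not yet been tested against placebo as a tocolytic. Maternal and neonatal harm are therefore central to the trial's own reasoning. A reader who follows the section literally would prepare an interim report without them. An imbalance in serious events between the arms would then not be part of the material on which continuation is formally decided.

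The trigger raises a smaller question. The trial asks whether withholding nifedipine is acceptably safe, so the interim result of most interest is placebo doing worse. A difference in either direction meets the rule equally. If the test is two-sided, part of its error rate is spent on the direction that does not threaten the women on placebo.

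**Working it through.** **Scope of the look.** Three statements, side by side:
- Interim analysis: the look covers the primary outcome and excludes everything else by its wording.
- Outcome measures: neonatal mortality, neonatal morbidity and maternal morbidity are secondary endpoints.
- Follow up of women and infants: neonatal complications are recorded.

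The excluded data are therefore collected anyway. The exclusion is written into the text. It is not a detail left to another document.

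**Inputs for the trigger.**
- Event rate 5%, which Sample size sets for the low-risk group: "we anticipate the probability on preterm birth within 7 days in the group of women with a negative fibronectine test and a cervical length 10-30". Background gives the pilot: "Amongst 19 women with a cervical length between 10-30 mm and a negative fibronectin test, only 1 woman delivered within 7 days", so 1/19 = 5.26%.
- Margin 7.5 points, so harm equal to the margin is 5% on nifedipine against 12.5% on placebo.
- 100 women randomised 1:1, taken as 50 per arm.
- Assumed, because the article does not state it: a two-sided 5% test.

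**The plan's own figure.** The article says "We need 220 fibronectin negative women in the cohort (110 per arm"). The formula is n per arm = (z₀.₉₅ + z₀.₈₀)² × 2p(1 − p) / margin².
- p = 0.05: (1.645 + 0.842)² × 0.095 / 0.005625 = 104.4, so 105.
- p = 1/19: 109.6, so 110.
- Power at 110 per arm with p = 0.05: Φ(0.075 / √(0.095/110) − 1.645) = Φ(0.907) = 81.8%.

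The stated size reproduces, so 5% and 7.5 points are the right inputs for the interim check.

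**What it takes to trigger.** With i events on nifedipine and j on placebo, z = ((j − i)/50) / √(2p̄(1 − p̄)/50), where p̄ = (i + j)/100. For 2 against 8, p̄ = 0.10 and z = 0.12/0.06 = 2.00, which passes 1.96; Fisher's two-sided p is 0.092, which does not. Fisher needs 2 against 10 (p = 0.028). With 3 on nifedipine, placebo needs 10 (chi-square) or 11 (Fisher).

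**Chance of triggering.** Sum the product of the two binomial probabilities over all (i, j) that reject, with 50 per arm:

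| Test, 5% level | 5% vs 5% | 5% vs 12.5% |
|---|---|---|
| Fisher, two-sided | 0.7% | 13.8% |
| Chi-square, two-sided | 4.3% | 25.7% |
| Fisher, one-sided for harm | 1.1% | 24.7% |
| Uncorrected z, one-sided for harm | 6.0% | 39.3% |

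The two-sided false alarms count both directions. Like for like, going one-sided gains 24.7 − 13.8 = 10.9 points (Fisher) or 39.3 − 25.7 = 13.6 points (uncorrected). The one-sided test still misses 61% to 75% of margin-sized harm.

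**Sensitivity.**
- At 5% against 20%, the two-sided test triggers in 51% (Fisher) to 66% (chi-square).
- With harm equal to the margin, the two-sided range is 15% to 30% at a 3% base rate and 12% to 22% at 8%.
- At the full 110 per arm, a two-sided test of 5% against 12.5% has 42% (Fisher) to 53% (chi-square) power.

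**The case against.** The strongest reply is that this is an article. Serious adverse event reporting, the committee's charter, and the level and sidedness of the interim test would normally sit in the full protocol, which is not shown. This largely stands. The missing level and direction are not a finding. A reader might also infer that the committee would never learn of deaths or maternal complications. The documents do not support that: the wording limits one formal comparison and does not deny the committee other information. The reply does not dispose of the scope itself, because the article states that restriction outright. Another document would have to add to it or override it.

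A second reply concerns the trigger. A two-sided test includes placebo being worse, a difference test can serve safety monitoring in a non-inferiority trial, and the committee decides rather than obeying a stopping rule. This stands too. A reader might go further and infer from the 14% to 26% that the rule can hardly ever fire, or that it gives false reassurance. That is too strong for three reasons. The figures rest on an assumed two-sided 5% test. Larger harm, 5% against 20%, triggers more often than not. And low power comes mainly from the numbers available at the interim, which is why a one-sided rule shares the weakness.

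Finally, 50 women per arm cannot support a powered comparison of deaths, and the article gives no event rates from which to compute one. That is correct. The case for showing these events rests on informed judgement by the committee.

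**Conclusion.** The point holds in a limited form. As written, the committee's formal interim analysis excludes neonatal death, neonatal morbidity and maternal side effects, all of which the trial records. This conclusion rests on the text alone and needs no numerical assumption. It does not extend to adverse event reporting outside the formal look.

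The direction of the trigger is secondary. Aiming it at harm from placebo would raise the chance of an alert at the margin from 14% to 25% with Fisher's test, or from 26% to 39% with the uncorrected test. This assumes 50 per arm, a 5% base rate and a two-sided 5% reading of the present rule. It is a modest gain. A futility rule is a design preference that nothing in the article requires, and its absence is not a fault.

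**What to change.** In Interim analysis, replace the restriction to the primary outcome with the primary outcome plus perinatal death, serious neonatal morbidity and serious maternal events, tabulated by arm and seen by the committee only. Many women will still be pregnant at that point, so the table should show how many in each arm have a known neonatal outcome. State that non-inferiority will not be claimed at the interim. The look then gives no extra chance of a positive claim, and the final one-sided 5% needs no adjustment. If the full protocol already sends these data to the committee, one sentence saying so is enough.

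As a secondary change, word the trigger as a guideline for harm, with placebo worse than nifedipine at a one-sided level and by a test fixed in advance, for example 5%. A futility guideline is optional.

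The cost is a few sentences in the protocol and the committee's charter, with no new data collection. The downside is a slightly higher chance of an unneeded alert for the committee to judge: about 1% with Fisher's test or 6% with the uncorrected test when the arms do not differ.
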